#### Primary outcome

##### Severity of BPD symptoms

The primary outcome variable is the reduction in severity of BPD symptoms from baseline to end of treatment assessed using the Borderline Personality Disorder Symptom Severity Index for Adolescents (BPDSI-IV-ado). The BPDSI-IV-ado is a semi-structured interview to assess the severity of BPD symptoms in adolescents and to detect short-term changes [46]. The BPDSI-IV-ado consists of 72 questions, spread over the 9 criteria for BPD. The total scale ranges from 0 to 90, and the subscales range from 0 to 10. The interview is designed to obtain detailed scores for each BPD symptom and to assess the severity of BPD symptoms over the past 3 months. The internal consistency of the BPDSI-IV-ado is moderate to high (Cronbach’s *α* ranging from 0.62 to 0.94) and the BPDSI-IV-ado has been demonstrated to be a reliable and valid instrument for the assessment of the severity of borderline symptoms in adolescents [46].

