### Sample size {14}

The sample size is determined by the predicted difference between the groups on the primary outcome, the BPDSI-IV-ado [46]. Consistent with previous studies on MBT for adolescents [43, 64] and MBT for adolescents compared with treatment as usual [27], we expect a medium effect size (Cohen’s *d* = 0.50) difference between MBT-early and CBT. Based on the BPDSI-IV-ado and with a two-sided *α* = 0.05, a power of 0.80 and a correlation of 0.50 between the repeated measures, based on Bales et al. [65] and Hutsebaut et al. [43], we require 59 participants in each treatment group (118 in total) with at least 1 follow-up measurement. Because of the vulnerable and unpredictable target population, we anticipate a 10% attrition rate and therefore intend to recruit at least 66 participants per group.

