## Statistical methods

### Statistical methods for primary and secondary outcomes {20a}

Data analysis will be conducted using SPSS Statistics. Treatment outcomes of the primary outcome, severity of BPD symptoms, over time will be examined using multilevel modelling. Multilevel modelling is able to model data from different time points, correcting for the dependency of observations by adding a within-subject correlation structure to the regression model. Another advantage of multilevel modelling is that it is able to handle missing data, by using the available data irrespective of the number of repeated measurements. In other words, adolescents with an incomplete number of follow-up measurements are also included in the treatment outcome analyses.

The interventions will be compared with the intention-to-treat adolescent sample, that is, with all adolescents randomized to either MBT-early or CBT.

A deviance test using restricted maximum likelihood will be used to assess whether random or fixed slopes should be assumed in models for each outcome variable. Subsequently, time will be included as appropriate (i.e. linear, logarithmic) and included in the model together with the treatment group and time by group interactions if likelihood ratio tests show significant improvement. The primary effect size of the treatments will be estimated from baseline to end of treatment and secondary effect sizes from baseline to 12-, 18-, and 24-month follow-up. Additional treatment offered in the follow-up period will be included as a covariate in the estimation of the multilevel models and effect sizes from baseline to 12-, 18-, and 24-month follow-up, as well as a predictor of treatment outcomes at 12-, 18-, and 24-month follow-up.

The secondary outcomes will be analysed similarly using multilevel modelling, in which the type of model is adapted to the outcome if needed (i.e. binary in case of the C-SSRS) from baseline to end of treatment, 12-, 18-, and 24-month follow-up. As noted, additional treatment offered in the follow-up period will be included as a covariate in the estimation of the multilevel models and effect sizes from baseline to 12-, 18-, and 24-month follow-up, as well as a predictor of treatment outcomes at 12-, 18-, and 24-month follow-up.

To examine the possible influence of missing data, we will repeat the analyses described using datasets in which missing data are imputed with state-of-the-art data imputation methods [66].

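### The term that carries the primary treatment effect enters the model only after a significant likelihood ratio test and only on a linear or logarithmic time curve, so the end-of-treatment estimate can be left out or understated

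*Protocol article*

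**What the plan says.** In the protocol article, the section on severity of BPD symptoms sets the estimand: "The primary outcome variable is the reduction in severity of BPD symptoms from baseline to end of treatment". Table 1 and section {18a} schedule the BPDSI-IV-ado interview three times: at baseline, end of treatment and 24 months.

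Section {20a} describes how the model is built. A deviance test first decides between random and fixed slopes. Then "time will be included as appropriate (i.e. linear, logarithmic"), and time is "included in the model together with the treatment group and time by group interactions if likelihood ratio tests show significant improvement". No categorical form of time is named. The next sentence of {20a} promises a primary effect size for the baseline-to-end-of-treatment interval and attaches no condition. It does not say how that figure is obtained if the interaction has been left out, or whether the primary model uses two or three visits.

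**The concern.** A confirmatory treatment effect should be estimated and reported with its interval whatever its p-value. Here the term that is the primary effect depends on a test.

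- If it is left out, any remaining group term is a constant difference averaged over visits that include baseline. That is a different quantity from the difference in change.
- If it is kept only because it was significant, the reported estimate is conditioned on significance and tends to be too large.

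The curve raises a separate problem. A linear or logarithmic function gives each arm one slope for three visits. It cannot represent a benefit that appears by end of treatment and then plateaus or fades, so the fitted end-of-treatment difference leans on the 24-month value.

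At stake are the size of the primary estimate and the existence of a prespecified confidence interval for it.

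**Working it through.** **Inputs from Sample size {14}:** "with a two-sided *α* = 0.05"; "a power of 0.80 and a correlation of 0.50 between the repeated measures"; "we expect a medium effect size (Cohen’s *d* = 0.50) difference between MBT-early and CBT"; "we require 59 participants in each treatment group (118 in total) with at least 1 follow-up measurement".

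**Assumptions not in the document:** end of treatment at month 4, 6 or 10 (no month is fixed; MBT-early has 16 weeks of intensive treatment plus a 6-month booster phase), compound symmetry, complete data, and the course of the effect to 24 months. The SD is set to 1.

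**The plan's own figure.** With correlation 0.50 the change score has SD √(2(1 − 0.5)) = 1, so n = 2(1.960 + 0.842)²/0.5² = 62.8, or 63 per arm. With baseline adjustment the variance factor is 1 − 0.5² = 0.75, giving 47.1, or 48. Neither gives 59. A slope formula comes to 58 or 59 only under particular assumed visit times. The attrition step does reproduce: 59/0.9 = 65.6, or 66. Nothing below depends on how 59 was derived; it is used only as the number per arm.

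**Step 1: the test alone, baseline and end of treatment only.**
- SE of the difference in change = √(2 × 1/59) = 0.184.
- True effect over SE = 0.50/0.184 = 2.716.
- P(significant at two-sided 0.05) = 77.5%, so the term is left out in 22.5% of trials.
- The term is kept when the estimate exceeds 1.96 × 0.184 = 0.361 in absolute value. The mean of a normal (0.50, 0.184) variable given this is 0.57.
- If a dropped term counts as zero, the overall mean is 0.775 × 0.571 = 0.44.
- Under no effect the term is kept in about 5% of trials.
- If the interaction is dropped and a group term stays, that term estimates (0 + 0.5)/2 = 0.25 SD with two visits, or (0 + 0.5 + 0.5)/3 = 0.33 SD with three visits and a sustained effect.

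**Step 2: the curve, three visits.** With compound symmetry and complete data, the slope of the group difference is b = Σ(t − t̄)δ/Sxx, where δ is the true difference at each visit. Its SE is √(2(1 − 0.5)/(59 × Sxx)), and the fitted end-of-treatment difference in change is b times the end-of-treatment value of t.

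Worked case: linear time, months 0, 4, 24, true differences 0, 0.5, 0.5.
- t̄ = 9.33; deviations −9.33, −5.33, 14.67; Sxx = 330.67.
- b = 0.5 × (−5.33 + 14.67)/330.67 = 0.0141 per month.
- Fitted difference at month 4 = 4 × 0.0141 = 0.056 SD, against a true 0.50.
- SE of b = √(1/(59 × 330.67)) = 0.00716; ratio 1.97; kept in 50.5% of trials.

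Same case with log(month + 1): t = 0, 1.609, 3.219; Sxx = 5.18; b = 0.5 × 1.609/5.18 = 0.155; fitted difference 0.155 × 1.609 = 0.25 SD.

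All cases have a true end-of-treatment difference of 0.50 SD. Cells show the fitted difference in SD and, in brackets, the percentage of trials in which the term is kept.

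| End of treatment, time | Sustained at 24 months | Halved (0.25) | Lost (0) | Grown (0.75) |
|---|---|---|---|---|
| Month 4, linear | 0.06 (50.5) | 0.01 (7.1) | −0.03 (20.3) | 0.10 (94.1) |
| Month 6, linear | 0.10 (58.5) | 0.03 (10.0) | −0.04 (14.0) | 0.16 (95.9) |
| Month 10, linear | 0.20 (72.3) | 0.09 (20.3) | −0.02 (6.0) | 0.30 (97.8) |
| Month 4, log | 0.25 (77.5) | 0.13 (27.4) | 0.00 (5.0) | 0.38 (98.3) |
| Month 6, log | 0.32 (82.2) | 0.18 (37.1) | 0.04 (6.6) | 0.46 (98.5) |
| Month 10, log | 0.40 (86.0) | 0.26 (49.5) | 0.11 (13.7) | 0.55 (98.5) |

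The log rows depend on the time unit. With log(day + 1), the sustained case gives 0.39 to 0.46 SD.

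**Step 3: the alternative.** With visit categorical and group-by-visit always in the model, the end-of-treatment contrast is unbiased at 0.50 SD in every column. With 59 per arm its power is 77.5% as a change contrast and 88.0% with baseline adjustment.

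**The case against.** A reader might infer that the primary effect will be dropped or misestimated. The document does not support that, for these reasons:

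- Section {20a} promises the baseline-to-end-of-treatment effect size without a condition. What it leaves is a conflict between two sentences, not a certain loss. This stands.
- A one-degree-of-freedom likelihood ratio test of the interaction is in effect the test of the treatment effect. With two visits it keeps the term as often as the direct contrast is significant (77.5%), and about 5% of the time under no effect. The dissemination section also commits to reporting null results. So the test costs neither power nor type I error. This stands, but it does not supply an estimate and interval when the term is left out.
- The sentence could mean that time, group and interaction are tested together, in which case general improvement could keep the interaction whatever its own significance. The wording allows this, and the ambiguity is itself a reason to rewrite it.
- Nothing says that the primary model includes month 24. With two visits any time function fits exactly and there is no curve bias. This stands. Equally, nothing restricts the model to two visits, and the same section speaks of outcomes over time and effect sizes to 24 months.
- The curve does not always do harm. With log time a sustained effect is detected at least as often as by the direct contrast (77.5% to 86.0%), and a growing effect is estimated at 0.38 to 0.55 SD. This stands.

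An article may leave model detail to a fuller plan. Here, however, it states a rule, and that rule does not secure the quantity the article defines as primary.

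**Conclusion.** The point holds in this form: followed as written, the rule can leave the primary effect out of the model or report it conditional on significance, and it conflicts with the unconditional promise in the next sentence. At the design effect with two visits, that means omission in about 22% of trials and a mean of 0.57 SD when kept, for a true 0.50 SD. These figures rest on the plan's own effect size, correlation and number per arm.

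If three visits are put on one curve, the end-of-treatment effect can also be understated when benefit plateaus or fades. That part depends on the assumed month of end of treatment, compound symmetry, the log time unit and the later course of the effect. Where the term is kept less often than the direct contrast would be significant, as with a halving effect, the cause is the curve and not the test. The defect in the wording needs none of these assumptions; only its size does.

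**What to change.** In section {20a}, or in the analysis plan before any outcome is compared by arm:

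1. Fit visit as a categorical factor (baseline, end of treatment and 24 months for the BPDSI-IV-ado), with group-by-visit in the model regardless of any test.
2. Name the end-of-treatment group contrast, with its 95% CI, as the single primary analysis.
3. Restrict deviance tests to the choice of random-effect or covariance structure.

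Secondary outcomes are to be analysed in the same way, so the same wording should cover them, with their own visits.

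The cost is a change of text and one or two degrees of freedom. No new data are needed.

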##### Provisions for post-trial care {30}

Throughout the treatment, the mental health professional will, in collaboration with the adolescent, evaluate whether the allocated treatment is sufficiently beneficial or if an alternative treatment might be more appropriate, either within the same mental healthcare institution or elsewhere. After dropping out or completing the allocated treatment, participants can also receive the non-assigned treatment (e.g. receiving MBT-early after completing CBT or vice versa). Based on the intention-to-treat principle, adolescents dropping out of the allocated treatment will be followed for research purposes, unless they withdraw their consent to participate in the follow-up assessments.

The sponsor has a liability insurance which is in accordance with Article 7 of the WMO (Medical Research Involving Human Subjects Act; in Dutch: Wet Medisch-wetenschappelijk Onderzoek met Mensen [WMO]). The risks of participating in this study are minimal. The interviews and assessments may be somewhat burdensome but do not carry specific risks. For this reason, the sponsor is dispensed from the obligation to provide insurance for participating in medical research by the Medical Research Ethics Committee (in Dutch: medisch-ethische toetsingscommissie [METC]) of the Erasmus Medical Center (MC).

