### Methods in analysis to handle protocol non-adherence and any statistical methods to handle missing data {20c}

Based on the intention-to-treat principle, adolescents will be analysed according to their assigned treatment and excluded from the analyses if they withdraw their consent after being randomized. There will be no replacement of adolescents after withdrawal. To examine the possible influence of missing data, we will repeat the analyses described using datasets in which missing data are imputed with state-of-the-art data imputation methods [66].

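### The secondary follow-up effects are adjusted for additional treatment that arises after randomisation, so the arm coefficient is not the effect of assignment, and no unadjusted follow-up estimate is stated

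*Protocol article*

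**What the plan says.** The section on statistical methods for primary and secondary outcomes {20a} declares the comparison: "The interventions will be compared with the intention-to-treat adolescent sample, that is, with all adolescents randomized to either MBT-early or CBT". The section on non-adherence and missing data {20c} agrees: "adolescents will be analysed according to their assigned treatment".

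Section {20a} then separates two sets of estimates: "The primary effect size of the treatments will be estimated from baseline to end of treatment and secondary effect sizes" for the 12-, 18- and 24-month follow-ups. For that second set it adds: "Additional treatment offered in the follow-up period will be included as a covariate in the estimation of the multilevel models and effect sizes". The same rule is repeated for the secondary outcomes. Both times, additional treatment is also named as a predictor of outcome at follow-up, which is a separate question.

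The article describes how additional treatment comes about. Under provisions for post-trial care {30}, the professional and the adolescent "evaluate whether the allocated treatment is sufficiently beneficial or if an alternative treatment might be more appropriate". The section continues: "After dropping out or completing the allocated treatment, participants can also receive the non-assigned treatment". The description of the MBT-early booster phase ties a possible new phase of care to progress judged at the final session.

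Table 1 places the BPDSI-IV-ado at baseline, end of treatment and 24 months only. The questionnaires are also collected at 12 and 18 months.

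**The concern.** A covariate measured before randomisation leaves the randomised comparison intact. One that arises afterwards, and can be changed by the arm, does not. Additional treatment lies on a path from allocation to later outcome: the arm affects response, response affects further care, and further care may affect the outcome. It also shares a cause with the outcome, because adolescents who remain more unwell are more likely to be given further care and to score worse later. Conditioning on it can therefore do two things at once. It takes out whatever part of the arm's effect runs through further care, and it compares adolescents with the same care history who differ in underlying severity between arms.

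The follow-up estimates carry real weight. The Discussion looks to longer-lasting benefit as a reason why MBT-early may be cost-effective. The Objectives expect non-inferiority on depression and anxiety, where a shift of either sign can change the conclusion. The economic evaluation is to follow the intention-to-treat principle, so the clinical and economic follow-up results would answer different questions.

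**Working it through.** No figure in the article depends on this choice, so there is none to reproduce. The check has a textual part and a numerical illustration.

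**Text.** Section {20a} fixes the covariate for the follow-up effects. Section {30} and the booster-phase description make that covariate depend on response, at least in part. Sections {20a} and {20c} declare analysis by assignment. The only repeat analysis is the one with imputed data, and section {20b} plans no additional analyses. So nothing in the article supplies a follow-up contrast without the covariate. The covariate is treatment offered rather than received, but either is determined after randomisation.

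**Model for the illustration.** Scores have SD 1 and correlation 0.50 between occasions (the correlation used in the sample size section). Allocation is 1:1, with 59 per arm for type I error. Let A = 1 for MBT-early and T = 1 for any additional treatment.

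- Uptake: logit P(T = 1) = α(arm) + β × severity.
- Follow-up score: Y = e − δA − γT, where e is the score without either effect (lower is better), δ is the arm's benefit apart from further care, and γ is the benefit of further care.
- Effect of assignment, as benefit: δ + γ × (p_MBT − p_CBT).
- Y is regressed on arm and baseline, with and without T.

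Usage rates, β, γ and the yes/no coding of T are assumptions. The regression at one follow-up stands in for the multilevel model.

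**Inert further care (γ = 0).** Here the effect of assignment and the direct effect both equal δ, so any departure from δ is bias. Adjusted estimates, as benefit of MBT-early in SD:

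| δ | Usage, CBT vs MBT-early | End-of-treatment severity, β = 0.75 | End-of-treatment severity, β = 1.5 | Mean of end-of-treatment and latent 24-month severity, β = 1.5 |
|---|---|---|---|---|
| 0.50 | 41% vs 28% | 0.485 | 0.47 | 0.42 |
| 0.30 | 56% vs 22% | 0.24 | 0.20 | 0.09 |
| 0 | 56% vs 29% | −0.05 | −0.08 | −0.17 |
| Type I error, δ = 0 | 56% vs 29% | about 6% | 7–8% | 17–19% |

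The smallest shift is 0.50 − 0.485 = 0.015, about 0.02 SD. The largest is 0.30 − 0.09 = 0.21, about 0.2 SD. Without the covariate, type I error is about 5%. Reversing the usage rates in the last column of the null row gives +0.17.

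**Further care that works (γ = 0.5).** With δ = 0.30 and usage 56% vs 22%, the effect of assignment is 0.30 + 0.5 × (0.22 − 0.56) = 0.30 − 0.17 = 0.13. The adjusted estimate is 0.20 (uptake driven by end-of-treatment severity, β = 1.5). It lies above the assignment effect of 0.13 and below the direct effect of 0.30, so it recovers neither.

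**One referral rule in both arms.** Here usage differs only because the arm changes end-of-treatment severity. With an arm effect of 0.5 SD at end of treatment and 40% usage after CBT, usage after MBT-early is about 26–31%.

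- δ = 0.50, γ = 0: adjusted 0.45 to 0.48 against 0.50.
- δ = 0.50, γ = 0.5: adjusted 0.455 to 0.48 against an assignment effect of 0.43 to 0.46.
- No arm effect on uptake: the two estimates agree.

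**The case against.** The strongest reply is that the trial's main result is not in question. The primary effect size runs from baseline to end of treatment, and the covariate is named only for later effects. A reader might infer that the primary result is biased; the article does not support that. A reader might also infer that the BPDSI-IV-ado is affected at three follow-ups; Table 1 shows only one, at 24 months. Both limits stand.

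Second, the intention-to-treat analysis set is kept: all randomised adolescents are analysed by assigned arm, and those who drop out of treatment are followed. It would be too strong to say that the population is broken. What is lost is the reading of the follow-up arm coefficient as the effect of assignment.

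Third, it is tempting to say that the adjustment shrinks the effect, or that the arm using more care fixes the direction. The checks show otherwise. With usage at 56% vs 22%, the estimate falls from 0.30 to 0.20 if further care is inert, and rises from 0.13 to 0.20 if it is worth 0.5 SD.

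Fourth, further care is not only for poor responders. Section {30} also says that "participants can also receive the non-assigned treatment (e.g. receiving MBT-early after completing CBT or vice versa"), without a non-response condition, and the booster-phase text leaves additional care to consultation with the family and team. Indication is therefore partial, and the larger shifts need strong indication.

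Finally, a separate analysis plan might add an unadjusted contrast. But this is not a detail left open: the article states the adjusted analysis twice.

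**Conclusion.** The point holds for the secondary follow-up effects: the BPDSI-IV-ado at 24 months and the questionnaire outcomes at 12, 18 and 24 months. As written, their arm coefficients are conditional on a response-dependent variable that arises after randomisation. They do not estimate the effect of assignment that the article declares, nor a valid direct effect.

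The size cannot be derived from the article. With inert further care and the assumed usage rates, it runs from about 0.02 to 0.2 SD, with type I error from about 6% to 19%. The upper end needs uptake to depend strongly on severity, including latent severity at 24 months. The bias is near zero if the arm leaves uptake unchanged, and its sign is not known in advance. This should be fixed before analysis, but it does not threaten the primary contrast.

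**What to change.** In section {20a}, at both places where the covariate is specified, state that the main 12-, 18- and 24-month between-arm contrasts are estimated without it, whatever further care was offered or received. For the BPDSI-IV-ado this means the 24-month contrast.

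Report additional treatment by arm descriptively and in the cost analysis. The covariate-adjusted model and the predictor analysis can stay as labelled supplementary analyses; the predictor question need not be dropped. If an effect in the absence of further treatment is wanted, define that estimand and use a method suited to it, such as inverse-probability weighting.

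The cost is a short change to the analysis text at two places and one additional set of model runs. It needs no new data, no more participants and no change to care.
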